### Study aims

The primary aim of the HEI is to generate a comprehensive biochemical roadmap detailing the human dose-response relationship between exercise and molecular activation. The HEI protocol presented in this report will first be completed with young, sedentary to normally active people, without comorbid diseases. Comprehensive blood profiling will facilitate the identification of circulating blood molecules within major biochemical molecular families (i.e., proteins, polar, moderately polar and lipid metabolites, non-coding RNAs) that are up- or down-regulated by acute bouts of exercise. Secondary aims include: 1.) the determination of the minimal intensity and duration of exercise required to induce a statistically significant change in blood concentration of exercise responsive molecules, 2.) the characterization of dose-response kinetics profiles for responsive molecules, 3.) the identification of immediate *versus* late molecular responses (i.e., molecules up- or down-regulated immediately post exercise *versus* the 60-minute recovery time point) and, 4.) the identification of sex-based differences in the exercise-dose biochemical response.

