**Fig 1 pone.0326149.g001:**
[figure not shown]
Experimental Visit Exercise Dose Protocol. Participants will perform a total of 10 experimental visits. N = 4 will be dedicated to the manipulation of exercise duration (i.e., variable duration at a constant intensity, *blue* box), N = 4 will be dedicated to the manipulation of exercise intensity (i.e., variable intensity at a constant duration, *green* box), and N = 2 will examine the impact of differential exercise modalities (i.e., up-right cycle ergometer, *red* box).

The four pre-specified exercise intensities will be defined as the speed and incline, individualized and confirmed for each participant during the baseline visit, required to elicit a percentage of V̇O_2_ at the first ventilatory threshold (VT1) as follows: 1.) V̇O_2_ of 30% below VT1 (VT1–30%), 2.) V̇O_2_ of 15% below VT1 (VT1–15%), 3.) V̇O_2_ of VT1, and 4.) V̇O_2_ of 15% above VT1 (VT1 + 15%). These intensities were chosen to ensure that each participant would be capable of completing at least 30 min of continuous exercise at the three lowest intensities. During the VT1 + 15% visit, participants will exercise to the point of volitional exhaustion. It is anticipated that the majority of participants will reach exhaustion within 30 min under these conditions. In cases where this does not occur, the incline of the treadmill will be gradually increased to ensure that exhaustion is reached within 5 additional minutes.

The four sessions dedicated to the modification of exercise duration will be comprised of fixed intensity exercise at VT1–15% for sessions of 10, 20, 30 and 60 min. This intensity was chosen to ensure that each participant will be capable of completing the longest duration session of 60 min. To examine differential biochemical responses as a function of exercise modality, participants will complete two 30-min sessions on an up-right cycle ergometer at a cadence of 60–80 revolutions per min, each performed at a V̇O2 corresponding to −30% and −15% of treadmill-assessed VT1. Gas exchange will be monitored during the first 5–10 min to ensure that the target V̇O_2_ is reached within 5–6 min. Each session will begin with a continuous 1 W/s ramp until 80% of the target V̇O_2_ is reached, after which individualized manual adjustments will be made to achieve the final workload that correlates with the desired V̇O_2_.

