#### Statistical analyses.

The Biomedical Data Science Center of the University of Lausanne and the Lausanne University Hospital (Lausanne, Switzerland) will oversee and coordinate all statistical analyses. It is anticipated that this work will generate a large database which will be amenable to conventional biostatistics and to rapidly evolving machine learning techniques. The theoretical basis for the following analyses is shown in Fig 3. Briefly, we hypothesize that measured molecules will conform to one of three specific response profiles: 1) up-regulated molecules, 2) down-regulated molecules, and 3) non-responsive molecules. Among molecules significantly up- or down-regulated by exercise, we further hypothesize that most will exhibit a distinct dose-response pattern, characterized either by a monotonic relationship (e.g., a linear correlation between molecular plasma concentration and exercise intensity and/or duration) or a threshold response. Threshold responsive molecules are anticipated to be unresponsive to low intensity and/or short duration intensity with subsequent up- or down-regulation occurring only in response to higher doses of exercise.

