**Fig 3 pone.0326149.g003:**
[figure not shown]
Hypothetical molecular exercise dose-response profiles. It is anticipated that the majority of plasma-based molecules will adhere to one of 3 primary exercise dose-response profiles: *Unresponsive* to exercise (A), *Up-regulated* by exercise (B), or *Down-regulated* by exercise (C).

Conventional analyses that will be applied are summarized as follows. The primary goal of the HEI is to identify the exercise intensity and duration dose thresholds of molecular activation or down-regulation. Thus, the primary outcome will be the discrete exercise intensity and duration that produces a statistically different molecular concentration compared to resting baseline conditions. Each participant will undergo 10 discrete resting blood samples (i.e., one prior to each acute bout of exercise). The concentration of each molecule under resting conditions will be used to calculate a participant-specific mean and standard deviation baseline concentration for each molecule. Levels of each molecule will then be similarly measured again from samples obtained immediately and 60-minute after each discrete dose acute exercise session. This will facilitate the generation of immediate post exercise and 60-minute post exercise curves that plot molecular concentration on the Y-axis and exercise dose on the X-axis.

For each participant, the resting molecular concentration will serve as their unique, participant-specific y-intercept, while the rate of change (slope) for each molecule will be assessed during escalating exercise intensity and duration. Mixed-effects linear (or generalized linear) models will be used to identify molecules that significantly change with exercise dose, using slope as a proxy in linear regression, and to determine the precise exercise dose at which the curve deviates from zero. This approach will allow us to pinpoint which molecules respond to exercise and at what intensity or duration each responsive molecule is up-regulated (positive change) or down-regulated (negative change). The potential application of more advanced machine learning techniques (e.g., for dimensionality reduction, regularization, etc.) will be determined in collaboration with the biostatistics team at a later stage, based on the size and characteristics of the final dataset.

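### The primary dose threshold is to come from a straight-line slope, which has none, and from a significance rule that for modest graded responses shifts with sample size and noise

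*Protocol article*

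**What the plan says.** All references are to the Protocol article.

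- **Goal.** Statistical analyses (text after Fig 3): "The primary goal of the HEI is to identify the exercise intensity and duration dose thresholds of molecular activation or down-regulation".
- **Primary outcome.** Same place: "the primary outcome will be the discrete exercise intensity and duration that produces a statistically different molecular concentration compared to resting baseline conditions". Study aims gives the minimal-dose version as a secondary aim: "the determination of the minimal intensity and duration of exercise required to induce a statistically significant change in blood concentration".
- **Model.** Mixed-effects linear or generalized linear models, with each participant's resting value as the intercept, "using slope as a proxy in linear regression, and to determine the precise exercise dose at which the curve deviates from zero". Only machine learning is put off to a later stage.
- **Expected shapes.** Statistical analyses says that most responsive molecules will show a pattern "characterized either by a monotonic relationship (e.g., a linear correlation between molecular plasma concentration and exercise intensity and/or duration) or a threshold response". For the second kind: "Threshold responsive molecules are anticipated to be unresponsive to low intensity", with "up- or down-regulation occurring only in response to higher doses of exercise".
- **Doses.** Experimental visits gives four intensities, and for duration "fixed intensity exercise at VT1–15% for sessions of 10, 20, 30 and 60 min".

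**The concern.** The quantity wanted is the dose at which a molecule starts to respond. Neither stated tool estimates that quantity in general.

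1. A line with a constant non-zero slope starting at the resting value departs from zero at every dose above rest. It has no break parameter, and it is the wrong shape for a molecule that is flat and then changes.
2. The lowest significantly different dose is a statement about detectability. It depends on effect, noise and number of participants together. A molecule that rises steadily from the first minute has no threshold, yet the rule will give it one.
3. With four tested doses per series, the data alone place a threshold between neighbouring doses. The promise of a precise dose goes further than that.

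The Discussion makes Phase 1 the comparator for later cohorts (older people, other ethnicities, athletes, patients). If those cohorts differ in size or in measurement noise, their thresholds could differ from Phase 1 with identical biology. The same section expects the results to help identify optimal exercise doses.

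**Working it through.** **Inputs.** From Sample size justification: n = 20, two-sided alpha 0.05, ρ = 0.6, more than 80% power at 1.2-fold, and a spread of ±0.12 not labelled as SD or SEM. From Statistical analyses: 10 resting samples per participant, averaged. From Experimental visits: durations 10, 20, 30 and 60 min. Assumed: compound symmetry, fold-change scale, and one unadjusted paired t-test per dose against the participant's resting mean.

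**Step 1, the plan's own figure.** For one resting and one post sample, SD of change = SD × √(2(1 − ρ)) = SD × √0.8.
- SD 0.12: 0.107, so 0.20/0.107 = 1.86 and power exceeds 99.9%.
- SD 0.339: 0.303, so 0.20/0.303 = 0.660 and power is 80%.

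The stated power therefore reproduces as a bound. An SD of 0.339 is the largest that still satisfies it, so 0.12 to 0.339 is used as the range.

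**Step 2, the straight line.** Take a response that is flat to 20 min and then rises to +0.44 at 60 min. The true changes at 10, 20, 30 and 60 min are 0, 0, 0.11 and 0.44. The least-squares slope through the resting value is (30 × 0.11 + 60 × 0.44)/(10² + 20² + 30² + 60²) = 29.7/5000 = 0.00594 per min. The fitted change at 20 min is 20 × 0.00594 = +0.12, where the truth is 0. With a free intercept and rest as a fifth point, the fit still gives +0.08 there. In simulation the slope is significant in about 100% of trials at n = 20. A clear slope thus says nothing about where the response begins.

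**Step 3, the significance rule on a line.** Against the 10-sample resting mean, SD of change = SD × √((1 − ρ)(1 + 1/10)) = SD × √0.44. That is 0.080 for SD 0.12 and 0.225 for SD 0.339. A linear response reaches about 50% power at the dose d* = t(0.975, n − 1) × SD of change / (√n × slope). For +0.10 at 30 min (slope 0.00333) and SD 0.339:
- n = 20: 2.093 × 0.225/√20 = 0.105, so d* ≈ 32 min.
- n = 80: 1.990 × 0.225/√80 = 0.050, so d* = 15 min.

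The apparent threshold falls roughly as 1/√n, although the response has none.

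**Step 4, simulated first significant duration.** The larger n only isolates the dependence on n; it is not a planned size.

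| Truth | SD | Outcome | n = 20 | n = 80 |
|---|---|---|---|---|
| Linear, +0.10 at 30 min | 0.12 | 10 min first | about 43% | 96% |
| Linear, +0.20 at 30 min | 0.339 | 10 min first | about 24% | 73% |
| Hinge at 20 min, +0.44 at 60 min | 0.339 | 60 min first | about 41% | 1% |
| Step of +0.20 between 20 and 30 min | 0.339 | 30 min first (correct) | 87% | 90% |
| Step of +0.44 between 20 and 30 min | 0.339 | 30 min first (correct) | about 91% | 90% |

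For the two steps, most of the error is false positives at 10 and 20 min: 1 − 0.95² = 9.75%.

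**Step 5, an estimator of the break.** A change-point fit to the hinge truth (SD 0.339) gave a median break of 20 min at both sizes, with 5th to 95th percentiles of 11–28 min at n = 20 and 17–24 min at n = 80. More participants narrowed the estimate without moving it. Under a linear truth the median estimated break was 0 at both sizes.

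**The case against.** The strongest reply has four parts.

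- **The rule often works.** A reader might infer that neither tool can locate any threshold, or that the reported thresholds will mostly reflect sample size. The documents do not support either. Abrupt steps that are large relative to noise are bracketed correctly at n = 20, with little change at higher n. How many molecules behave that way, and with what effect-to-noise ratio, is not stated.
- **The example protein may be unaffected.** If BDNF is linear to 1.44-fold at 30 min, 10 min is first significant at n = 20 in about 79% of trials with SD 0.339 and in practically all with SD 0.12. The drift is then small or absent. Nor does the protocol say that retention will range from 20 to 30: it plans 20 completers from 30 recruited. Sizes below 20 have no basis in it.
- **The definition is operational.** The outcome speaks of discrete doses and openly means a significant change. Monotonic and threshold responders are named as separate classes, and dose-response profiles are a secondary aim, so one cannot say that every linear molecule will be published with a threshold. This stands as far as it goes. Even so, the text names these doses as thresholds of activation, and no step in it withholds a threshold from a linear molecule.
- **The article only summarises the analysis.** It leaves open whether dose is continuous or a factor, and a factor fits within a linear mixed model. That would repair the shape problem, but the significance rule would remain. That rule is written into the primary outcome, so it is more than detail left for later.

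**Conclusion.** The point holds for graded responses that are modest relative to noise. For these, the stated outcome measures the smallest detectable dose at a given n and noise level, and the straight line cannot supply the missing threshold. In the examples, a fourfold change in n moves the share of trials with 10 min as first significant duration from about 43% to 96%, or from about 24% to 73%, with the truth unchanged. For a real hinge, 60 min comes first, so that the bracket is wrong, in about 41% of trials at n = 20. For steps that are large relative to noise the rule is adequate.

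The sizes rest on ρ = 0.6, compound symmetry, an assumed SD between 0.12 and 0.339, and the chosen response shapes. They illustrate the mechanism and do not predict the share of molecules affected. That a constant slope has no break needs none of these assumptions.

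**What to change.** In Statistical analyses:

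1. Enter dose as a factor (rest plus the four doses of each series) and report the change at each dose with its confidence interval.
2. For each molecule, compare null, linear and single-change-point fits by a criterion fixed in advance. Report a threshold only where the change-point fit is preferred, and call the others linear or unresponsive.
3. Report the threshold as the bracket between adjacent tested doses, or as the estimated break with a bootstrap interval. Alternatively, report the dose at which the fitted curve reaches a minimum fold change stated in advance. One resting SD is not a suitable margin, although the plan already computes it, because it grows with assay noise.
4. Replace the significance wording in the primary outcome, and the promise of a precise dose, with this definition.

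No new visits or samples are needed. The cost is some extra computing, and thresholds that look less sharp.

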#### Sample size justification.

Sample size calculations are based on a proposed sample size of n = 20. Given the time requirements for participants and our prior experience with similar studies, we anticipate a 2:1 attrition rate and have planned for the recruitment of 30 participants. For sample size calculations, alpha was 0.05 and 2-tailed. Power is sensitive to the positive correlation between repeated measures of the outcome variables over time, denoted by ρ, with greater correlation reducing the variance. The plasma protein brain derived neurotrophic factor (BDNF), based on prior work characterizing this protein as being moderately responsive to exercise (i.e., 1.44 ± 0.12 fold change following 30 min of moderate intensity exercise) [24], was used for calculations. We used previously published data to estimate conservatively ρ as 0.6 for the candidate variable [24]. Accordingly, we will have >80% power to detect differences between baseline (resting) and immediate post-peak exercise (post) for the moderately exercise-responsive protein BDNF as low as 1.2-fold change. Importantly this magnitude of change falls well below what we anticipate seeing given the proposed stimulus intensities and duration.

## Discussion

This report summarizes the rationale, study design, and experimental protocols of the Human Exersome Initiative (HEI) which was created with an overarching aim of defining dose-response relationships between exercise and human biochemistry. Coupling carefully controlled laboratory-based exercise sessions at discrete exercise intensities and durations with advanced molecular profiling, we aim to develop a comprehensive list of exercise responsive molecules and to determine the specific intensity and/or duration of exercise required for significant up- or down-regulation. The HEI protocol described here will first be applied to healthy young men and women (Phase 1). Data derived from Phase 1 will broadly define the dose-dependent nature of exercise on human plasma-based biochemistry. We anticipate that data from Phase 1 will facilitate biomarker discovery, molecular pathway discovery, and the identification of optimal exercise doses for use in future studies and clinical interventions.

The broader overarching goal of the HEI is to elucidate how the human exercise dose response varies as a function of human phenotypic variability. Following completion of the initial work focused on young healthy people, we plan to extend this protocol into additional human cohorts including people of older age (65–80 years), people of different ethnicities, trained athletes, and clinical populations with common comorbid diseases. For each of these iterations, Phase 1 data characterizing the molecular exercise response among healthy young people will serve as the comparator for subsequent iterations of the protocol. The identification of how molecular responses differ as a function of human phenotypic variability will provide novel insights into the biochemistry of functional decline (i.e., with older age or the development of common forms of co-morbid disease) and among people with supra-normal exercise capacity (i.e., trained athletes). It is anticipated that these subsequent phases of the HEI will elucidate biochemical mechanisms underlying changes in human exercise capacity across the lifespan and set the stage for the development and refinement of age-specific exercise interventions and guidelines, nutritional supplements, and pharmaceutical compounds that may ultimately attenuate the functional decline.

The HEI was designed to define biochemical responses to acute bouts of exercise. It is recognized that the HEI will not address molecular adaptations to exercise training. Ongoing work within the MoTrPAC will provide important information that will complement data emerging from the HEI [16]. While the rationale and protocol of MoTrPAC have been carefully vetted and described, this project includes a single dose of endurance exercise which may exceed or fall short of exercise doses required for specific biochemical regulation. Accordingly, it is anticipated that the identification of specific exercise doses that are required to stimulate specific molecular responses will permit optimally informed design of future training studies and clinical interventions that will target specific outcomes.
